#### **Inclusion of Women and Minorities**

We have no exclusion criteria regarding gender or ethnicity.

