Current studies on EC vapors are conflicting and reveal that they produce either similar (19-21) or reduced (6, 22) effects on systemic nicotine levels, carcinogen levels and cardiovascular effects compared to other nicotine replacement strategies. Side effects of ECs include mouth/throat irritation (23), vertigo (23), headaches (23), bronchospasm (8, 24) and nausea (25) similar to those found with approved nicotine replacement therapies (NRT).

ECs produce nicotine vapors of a particle size that deposit the vapor in the lower respiratory tract (26, 27), unlike the larger sized particles of approved inhalation NRT devices that remain in the oropharynx (28, 29). This fact may explain why EC vaping but not NRT use has been associated with lipoid pneumonia (30) and bronchospasm (8, 24). It raises concerns that the toxicity of components of EC such as diluents may have significant health risks (31), in addition to the known risks of nicotine alone (32). The lack of consistent results demands a full evaluation of EC toxicity.

In 2009, the FDA reported that a cartridge of an electronic cigarette contained diethylene glycol (33), even though other studies failed to identify this substance. The FDA testing also identified

[name] PI

ADVERSE AIRWAY EFFECTS OF INHALED NICOTINE FROM TOBACCO AND E-CIGARETTES

VERSION 3.3 09/28/2017

tobacco-specific nitrosamines in ECs (33). Both substances are known carcinogens. However, they can also be found in nicotine gums and nicotine inhalers (34). Other harmful substances were found as well, including acrolein (35). The French national consumer agency analyzed the vapor of ECs and found formaldehyde levels matching those from tobacco cigarettes (36). On the other hand, the test conditions did not necessarily mimic real life scenarios. Therefore, exposure systems mimicking real life situations with an appropriate evaluation of toxicity are desperately needed, especially since the use of ECs has increased dramatically in recent years. Our proposal is designed to answer this question by investigating the safety of ECs in primary cultures of normal human bronchial epithelial (NHBE) cells and in clinical trials with individuals who are non-smokers or who replace tobacco smoking with EC vaping.

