#### EXPERIMENTAL DESIGN

The design is a smoking replacement trial, in which we will compare changes in upper airway ion transport and inflammation in smokers who switch to EC vaping versus subjects that continue to smoke tobacco cigarettes. In addition, we will use the trial design to evaluate the feasibility of using the EC as a means to quit tobacco use.

*Study population/recruitment.* We plan to study the effects of continuous EC vaping (3 months) in 30 active smokers that successfully switch to ECs (a smoking replacement trial). For this, we plan to enroll approximately 200 active smokers (screening phase), expecting that only one fourth will be able to stay abstinent from tobacco and keep exclusively vaping the ECs after a month. The 30 subjects who can remain tobacco-smoke free for the initial 4 weeks will undergo the study procedures, as >90% of them are likely to remain on ECs for the next few months (49) (as opposed to what is observed in a smoking cessation trial (48)). Twenty additional smokers who wish to continue to smoke will be enrolled as well for the comparator group. Subjects that actively smoke and have a history of at least 5 pack-years will be invited to participate. Exclusion criteria include HIV, marijuana use, COPD, asthma and other concomitant inflammatory pulmonary disorders, subjects with known pulmonary diseases including malignancies, subjects with prior thoracic surgery and subjects that used oral corticosteroids or antibiotics within the prior 3 months, subjects with allergies to study medications and subjects incapable of providing informed consent. Subjects must be in stable condition.

Subjects will be enrolled primarily in the pulmonary function test laboratory, pulmonary and primary care clinics. We will place IRB-approved advertisements in clinics if necessary. Recruitment will occur over a course of 5 years.

The study will have 4 Phases: transition, stability, weaning and surveillance.

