*Phase I: transition from tobacco use to EC (4 weeks):* After signing informed consent, all subjects entering the screening phase will have pulmonary function testing (PFT) if none available in the prior month and we will record basic demographic and social history. After obtaining an initial blood sample (plasma), we will provide and instruct the subjects how to use the EC (eVic®). The nicotine content of the “e-liquid” provided (a PG:VG mix 50:50) will match the number of cigarettes smoked a day and will vary from subject to subject (see below for calculation). We will use the 12 mg/ml concentration e-liquid. During this “transition phase” period we will assess their success of abstaining from smoking tobacco. To monitor abstinence to tobacco smoking, subjects will be seen in person weekly for measurements of exhaled CO (ExCO), and venous COHb. ExCO > 6 ppm (50) or venous COHb >1.6% (51) will be considered the result of tobacco cigarette use. In addition, we will measure urinary marijuana with a qualitative test and if positive we will exclude the subject from the study. During those visits we will assess vaping compliance by downloading the vaping history of the EC using the myVapors® software, available from the EC manufacturer and will collect data regarding potential side effects. Subjects will be encouraged to transition solely to EC within the first 4 weeks. Blood draws for biomarker assessment will be performed in each visit of this phase.

*Phase II: Stability on EC (12 weeks):* In this phase, subjects will remain on EC use for three months. In this phase, all subjects will continue to use ECs at a stable nicotine concentration for additional 12 weeks. Tobacco use abstinence will be monitored every week as in the transition phase as detailed in Table 1. High ExCO levels will be confirmed with venous COHb if necessary. Oral washes and nasal lavages will be done at the beginning and the end of this phase.

Smoker controls: 20 tobacco smokers will be directly enrolled in the “stability” phase, where they will continue to use their regular tobacco for 3 months. They will undergo nasal samplings and NPDs before and after, with monthly blood collections. After this phase, these control subjects may be re-enrolled in the study to start in the transition phase with EC.

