### 1. Risks to the Subjects

A) Human Subjects Involvement and Characteristics: We will enroll active smokers older than 18 years, who actively smoke and have a smoking history of at least 5 pack-years. These subjects should not be currently using ECs but should be willing to replace tobacco cigarettes to ECs. All subjects will undergo lung function testing to exclude chronic obstructive pulmonary disease, as this condition may not only increase the risk of procedures but also impose additional inflammatory confounders. Exclusion criteria include the presence of airflow obstruction ( $FEV_1/FVC < LLN$ ), other concomitant inflammatory pulmonary disorders (i.e asthma), subjects with known pulmonary malignancies, subjects with prior thoracic surgery and subjects that used oral corticosteroids or antibiotics within the prior 3 months, subjects with allergies to study medications and subjects incapable of providing informed consent. Subjects must be in stable condition. Considering that about 75% will not be able to stay abstinent from tobacco cigarette smoking, we expect to screen 120 subjects, who meet these criteria, to be able to have 30 subjects who will complete all study procedures 3 months apart. In addition, we will enroll 20 active smokers unwilling to quit tobacco smoking but willing to undergo the study procedures using the same exclusion criteria. Since these trials will be performed at the Miami Veterans Affairs (VA) Medical Center, we expect that subjects will be >90% men, 20% Hispanic and 25% African American.

B) Sources of Materials: The following are the procedures that will be performed:

Collection of nasal lavage fluid: Nasal lavage fluid will be used to measure changes in epithelial inflammatory cytokines. The lavage will be performed using saline pre-warmed to 37°C. The subject will keep the head bent forward with the face held horizontally, while the left nasal cavity is filled with saline, using a 10 ml syringe connected to the nostril via a short tube and a nasal olive. After 5 minutes approximately 5 ml of the saline is recovered by aspiration. The samples will be centrifuged to remove cellular debris and aliquots of the supernatants stored at -20°C in microcentrifuge tubes until analysis.

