Pulmonary Function Testing is a routine clinical procedure with few risks. Patients are coached to make repeated forceful breathing efforts. The subjects might have chest soreness. Unusually, subjects may become lightheaded during these efforts. We will minimize this risk by having the PFT done in a sitting position.

EBC collection: may produce dizziness if the subject hyperventilates. We will minimize this risk by coaching subjects to keep a slow and paced respiration.

Electronic cigarettes: Known side effects of ECs include mouth/throat irritation (23), vertigo (23), headaches (23), bronchospasm (8, 24), and nausea (25) similar to those found with approved

nicotine replacement therapies (NRT). Other potential toxic effects are unknown and the goal of this proposal.

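### Neither exclusion list addresses pregnancy or breastfeeding and Table 1 has no pregnancy check, although women are eligible and the study supplies nicotine e-liquid

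*Protocol*

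**What the plan says.** The protocol gives its exclusion criteria twice. Under Experimental Design the list begins "Exclusion criteria include HIV, marijuana use, COPD, asthma and other concomitant inflammatory pulmonary disorders". It goes on to other lung disease, thoracic surgery and recent oral corticosteroids or antibiotics, and closes with "subjects with allergies to study medications and subjects incapable of providing informed consent. Subjects must be in stable condition". Under Human Subjects, section 1 (Risks to the Subjects), a second list begins "Exclusion criteria include the presence of airflow obstruction" and closes in much the same way, with "subjects with allergies to study medications and subjects incapable of providing informed consent".

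On women, section 1 expects more than 90% of subjects to be men, and the section Inclusion of Women and Minorities states "We have no exclusion criteria regarding gender or ethnicity". Inclusion requires age above 18 and at least 5 pack-years, with no condition on childbearing potential.

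On exposure, Phase I supplies 12 mg/ml nicotine e-liquid, and Table 1 shows a refill at every visit from enrolment to V16. Of EC effects beyond the listed side effects, Potential Risks says "Other potential toxic effects are unknown and the goal of this proposal". Protection Against Risk adds that subjects will be told the risks are not well established.

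On testing, Phase I says "we will measure urinary marijuana with a qualitative test". Table 1 places that screen at enrolment, V4 and V16.

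**The concern.** The study gives participants an inhaled nicotine product whose toxicity it sets out to measure. Eligibility is the point at which a protocol decides who may be exposed to that uncertainty. Whether a pregnant or breastfeeding smoker should be among them is a decision this protocol does not make in any visible section.

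Two consequences follow. Site staff applying either list would find nothing that stops them enrolling a pregnant woman. If a participant became pregnant during follow-up, no scheduled procedure would detect it and no stated rule would say what happens next. What is at stake is participant safety and consistent handling across cases. No endpoint, power figure or analysis is affected.

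**Working it through.** The plan states no figure to reproduce. The check is a side-by-side reading, followed by an upper bound on the number of women concerned.

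**Where a pregnancy provision could stand**

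| Place in the protocol | What it covers | Pregnancy or breastfeeding |
|---|---|---|
| Experimental Design, exclusion list | HIV, marijuana, lung disease and malignancy, thoracic surgery, recent steroids or antibiotics, allergy, inability to consent | Not mentioned |
| Risks to the Subjects, exclusion list | Airflow obstruction, inflammatory lung disease, lung malignancy, thoracic surgery, recent steroids or antibiotics, allergy, inability to consent | Not mentioned |
| Table 1 | Exhaled CO, COHb, marijuana screen, nasal procedures, lung function, plasma and others | No check scheduled |
| Potential Risks; Protection Against Risk | Risks of each procedure and of ECs | Not mentioned |
| Data Safety and Monitoring Plan | Adverse event review; stopping for individual side effects | Not mentioned |
| Inclusion of Women and Minorities | No restriction by gender or ethnicity | Not mentioned |

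The two lists also differ from each other: HIV and marijuana use appear only in the first. A criterion added to one list alone would therefore leave the other silent.

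**How many women**

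Inputs:
- Share of women: below 10%, since more than 90% men are expected (Risks to the Subjects).
- EC starters: 120 (Risks to the Subjects and the Planned Enrollment table) or about 200 (Experimental Design). The protocol gives both figures, so both are carried through.
- EC completers: 30 (both sections).

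Formula: upper bound = 0.10 × number of participants.

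- 120 starters: 0.10 × 120 = 12, so fewer than 12 women.
- 200 starters: 0.10 × 200 = 20, so fewer than 20 women.
- 30 completers: 0.10 × 30 = 3, so fewer than 3 women, assuming that women and men complete at the same rate.

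**How long**

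Scheduled EC use is 4 weeks of transition plus 12 weeks of stability, 4 + 12 = 16 weeks. That applies to the roughly 30 who switch successfully. The plan expects the other three quarters to fail the 4-week transition.

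**What the existing urine samples allow**

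The marijuana screen provides urine at enrolment, V4 and V16. The enrolment sample can precede the first e-liquid. V4 and V16 are 16 − 4 = 12 weeks apart, so these samples alone would leave most of the stability phase unchecked.

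**The case against.** The case on the other side has several parts, and much of it stands.

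- **The absence is not fully proven.** Title and consent pages are not in the text available for review, and both lists introduce their items as included rather than exhaustive. Wording elsewhere cannot be ruled out. Even so, the two operative lists and the visit schedule are visible and silent, and a safety criterion held elsewhere would still need to reach them.
- **A reader might infer that the statement on gender is the defect, or that the plan directs enrolment of pregnant women.** The text supports neither. Having no gender exclusion is compatible with a pregnancy criterion. The general requirements of stable condition and of selecting people who tolerate the procedures leave staff some discretion. The supported claim is narrower: the visible criteria do not bar a pregnant smoker.
- **A reader might take the supplied nicotine as a new exposure.** Every candidate already smokes, and the dose calculation section aims to match the previous daily nicotine. The EC replaces tobacco. What remains is the EC-specific toxicity that the protocol calls unknown.
- **A reader might add the nasal potential difference (NPD) agents as a further hazard.** Potential Risks describes the amiloride and isoproterenol doses as low, with no or negligible systemic absorption expected. Table 1 schedules NPD only at V5 and V16. This adds little.
- **A reader might count women among all recruits.** Adding the 20 smoker controls gives fewer than 14 of 140 or 22 of 220. Controls receive no EC unless they later re-enrol, so the EC-starter counts are the right ones for EC exposure.
- **The documents do not describe a hazard specific to pregnancy.** The reference behind the known risks of nicotine is a policy statement on smokeless tobacco and cardiovascular disease. The point rests on the protocol's own account of the EC risks as unestablished, not on a quoted fetal risk.

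The statistical analysis plan does not answer the point: eligibility and safety screening belong in the protocol.

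**Conclusion.** The gap is real and its weight is modest. Neither visible exclusion list addresses pregnancy or breastfeeding, Table 1 has no check, and the safety plan defines no action for a pregnancy during the study. Meanwhile women are eligible and the study supplies a nicotine product of admittedly uncertain risk.

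The women concerned number fewer than about 12 or 20 at the start of EC use, depending on which planned total applies, and fewer than about 3 over the full 16 weeks. These are bounds on all women; the documents do not give the share who could be pregnant. The conclusion assumes that the pages not available for review contain no such provision and that the expected proportion of men is about right. It deserves correction because the correction costs almost nothing and decides who is exposed.

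**What to change.** Add a criterion on pregnancy and breastfeeding to both exclusion lists, in identical words. Add a pregnancy check to Table 1 at enrolment, before any e-liquid is dispensed, using the urine already collected for the marijuana screen; the samples at V4 and V16 are also available. State what happens if a pregnancy begins during the study. Because the V4 and V16 samples leave a 12-week interval, say whether anything is done in between. The content of the rule, including how a pregnancy during the study is handled, is for the sponsor and the IRB. If a provision already exists in pages not shown, carry it into both lists and Table 1.

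The cost is one line in each list, one row in Table 1 and a dipstick on urine already in hand. A few women may become ineligible.

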#### **Inclusion of Children**

Although possible, the inclusion criteria of having at least 5 years of smoking makes it unlikely that children (aged between 18 and 21) will be enrolled.

